## Abstract

**Background:**

Acute respiratory failure (ARF) is still one of the most severe complications in immunocompromised patients. Our previous systematic review showed noninvasive mechanical ventilation (NIV) reduced mortality, length of hospitalization and ICU stay in AIDS/hematological malignancy patients with relatively less severe ARF, compared to invasive mechanical ventilation (IMV). However, this systematic review was based on 13 observational studies and the quality of evidence was low to moderate. The efficacy of NIV in more severe ARF and in patients with other causes of immunodeficiency is still unclear. We aim to determine the efficacy of the initial ventilation strategy in managing ARF in immunocompromised patients stratified by different disease severity and causes of immunodeficiency, and explore predictors for failure of NIV.

**Methods and analysis:**

The VENIM is a multicentre randomized controlled trial (RCT) comparing the effects of NIV compared with IMV in adult immunocompromised patients with severe hypoxemic ARF. Patients who meet the indications for both forms of ventilatory support will be included. Primary outcome will be 30-day all-cause mortality. Secondary outcomes will include in-hospital mortality, length of stay in hospital, improvement of oxygenation, nosocomial infections, seven-day organ failure, adverse events of intervention, et al. Subgroups with different disease severity and causes of immunodeficiency will also be analyzed.

**Discussion:**

VENIM is the first randomized controlled trial aiming at assessing the efficacy of initial ventilation strategy in treating moderate and severe acute respiratory failure in immunocompromised patients. The result of this RCT may help doctors with their ventilation decisions.

**Trial registration:**

ClinicalTrials.gov NCT02983851. Registered 2 September 2016.

## Background

Immunocompromised patients has increased subtantially over recent decades because of the epidemic of Acquired Immune Deficiency Syndrome (AIDS), common use of solid and hematologic transplantation requiring subsequent immunosuppressive therapy, better and thus greater use of iatrogenic immunosuppression, and improved survival due to better health care conditions [1]. Infection, especially pulmonary infection, is still one of the most common complications of immunosuppression [1]. Acute respiratory failure (ARF), especially when induced by sepsis, is the leading cause of ICU admission in immunocompromised patients, with a case fatality, between 30% and 90%, despite the use of antimicrobial agents and preventive measures [1–6].

Noninvasive mechanical ventilation (NIV) and invasive mechanical ventilation (IMV) are two fundamental treatment ways to provide supplemental oxygen and ventilatory support for patients with relatively severe ARF. NIV is the delivery of positive pressure ventilation via oronasal or nasal airway, a total face mask or helmet rather than endotracheal tube. The most common types of NIV are continuous positive airway pressure (CPAP) and bi-level positive airway pressure (BIPAP). By avoiding invasive intubation or tracheostomy, NIV keeps an intact upper airway and therefore retains airway defense mechanisms, which is important for immunocompromised patients who are especially vulnerable to nosocomial infections. Common complications caused by intubation such as aspiration pneumonia, ventilator-associated diseases, and trauma to adjacent organs could thus be avoided by NIV [7, 8]. NIV is now generally considered as the first-line intervention for several ARF subtypes [9–11], including chronic obstructive pulmonary disease (COPD), asthma, cardiogenic pulmonary edema and other situations [12]. However, NIV is not appropriate for all forms of ARF. In ARDS patients, for instance, the use of NIV is controversial and lacking high-quality of evidence [13–16]. Another oxygen therapy named high-flow oxygen therapy is getting more and more attention in critical care. Recent studies showed high-flow oxygen therapy obtained a comparable or even better prognosis in ARF patients [17–19]. However, it requires more advanced equipment, thus not as popularized as other conventional oxygen therapies especially in developing countries.

Two indications have been mainly considered for NIV in patients with relatively severe ARF: (1) alternative to IMV when ARF patient has contraindications to IMV, and (2) to avoid IMV when ARF patient has not yet met the criteria for intubation [20]. Generally, indications for NIV treatment include increased dyspnea (moderate to severe), tachypnea (with respiratory rate > 24 breaths per min in obstructive or >30 per min in restrictive), the use of accessory muscles, or paradoxic abdominal movements. Other indications include acute or acute on chronic ventilatory failure with hypercapnia and respiratory acidosis (PaCO_2_ > 45 mmHg and pH <7.35) and/or hypoxemia PaO_2_/FiO_2_ ratio < 200 [8]. Respiratory arrest and inability to fit the mask are considered absolute contraindications to NIV. Relative contraindications include: medically unstable (e.g. shock, uncontrolled cardiac events and uncontrolled upper gastrointestinal hemorrhage), uncooperative and agitated, uncontrolled excessive secretions, multiple organ failure, recent upper airway surgery [8].

NIV is not appropriate for all immunocompromised patients with ARF either [21, 22]. Efficacy of NIV on patients depends on disease severity, causes of immunodeficiency and forms of ARF. It’s critically important to select target patients carefully. Recently, we and our collaborators conducted a systematic review and meta-analysis [21] based on 13 observational studies (2552 patients). The study showed NIV could significantly reduce mortality, duration of hospitalization/ICU stay, and nosocomial infections mainly in less severe (reflected by the Simplified Acute Physiology Score II [23], SAPS II < 60), AIDS, and hematological malignancy subgroups, with quality of evidence from very low to moderate. However, NIV didn’t show any significant advantages over IMV in relatively more severe patients [21]. To our knowledge, evidence for other causes of immunodeficiency and different types of ARF is lacking. Early recognition of failure of NIV is also important for prognosis in these patients. Several predictors of NIV failure have been proposed to be used in immunocompromised patients, such as higher disease severity, higher respiratory rate under NIV, delayed initiation of NIV treatment, need for vasopressors or renal replacement therapy [24]. However, the cut-off point of transferring NIV to IMV in these patients is still unclear [25].

The primary goal of the present multicentre randomized controlled trial is to assess the efficacy of the initial ventilation strategy, NIV or IMV, in managing severe hypoxemic ARF in immunocompromised patients. The secondary goal of this trial is to assess the effect of NIV or IMV in patients stratified by different disease severity, causes of immunodeficiency, and presence of predictors for failure of NIV.

## Methods

### Design

The present trial is a multicentre, open-label, parallel-group randomized controlled trial of the initial **ven**tilation strategy for adult **im**munocompromised patients with severe acute hypoxemic respiratory failure (**VENIM**).

### Study setting

The VENIM trial will be conducted in the resuscitation rooms and intensive care units (ICUs) of Emergency Department in seventeen hospitals in China, including Peking Union Medical College Hospital, Fujian Provincial Hospital, The First Affiliated Hospital of Kunming Medical University, The First Affiliated Hospital of Sun Yat-sen University, Renmin Hospital of Wuhan University (Hubei General Hospital), The First Affiliated Hospital of Zhengzhou University, Jiangsu Province Hospital (The First Affiliated Hospital of Nanjing Medical University), The Second Hospital of Hebei Medical University, The First Affiliated Hospital of Anhui Medical University, The Affiliated Hospital of Guizhou Medical University, Affiliated Hospital of Inner Mongolia Medical University, General Hospital of Ningxia Medical University, Tianjin Medical University General Hospital, The Second Xiangya Hospital of Central South University, The Second Affiliated Hospital of Harbin Medical University, Cangzhou Central Hospital in Hebei province and Handan First Hospital in Hebei province. These are all tertiary level hospitals in China providing full-spectrum health services to critical patients. Referrals are from throughout China. In each hospital, staffs have been trained in the study procedures and protocols of NIV or IMV management.

### Study population

Patients will be recruited in hospitals where the staffs have considerable experience and expertise in the treatment of immunocompromised patients and application of mechanical ventilation. The inclusion and exclusion criteria are as followings (Table 1):

**Table 1 Tab1:** Inclusion and exclusion criteria

Population characteristics	Inclusion criteria	Exclusion criteria
Demographic characteristics	Adult (18 years old ≤ age ≤ 80 years old) immunocompromised patients with moderate to severe ARF diagnosed within the last 72 h.	Age < 18 or >80 years old.
Diagnosis of mid to severe ARF	85 ≤ PaO_2_/FiO_2_ ≤ 170 adjusted with altitude change or clinically diagnosed with evidence of respiratory distress (intercostal recession or other assisted breathing muscle movements, polypnea >35/min or dyspnea at rest).	(1) Partial pressure of arterial carbon dioxide (PaCO_2_) > 50 mmHg or arterial pH < 7.20; (2) PaO_2_/FiO_2_ > 170(mild) or PaO_2_/FiO_2_ < 85(severe);
Diagnosis of immunocompromised status	At least one of the following: (1) Hematologic malignancy or solid tumor under chemotherapy; (2) Solid organ or stem cell transplant; (3) Long-term (>30 days) and high dose steroids (>1 mg/kg/d prednisone equivalent) usage and/or any other immunosuppressive drugs; (4) Neutropenia (defined as a neutrocyte count of <1.0 × 109/L) showing for at least 48 h.	Other causes of immunocompromise including HIV infection, etc.
Indications for intervention	Patients with severe ARF described above, in which mechanical ventilation is indicated.	Patients have been treated with NIV, IMV or high-flow oxygen therapy within 30 days. NIV is contraindicated or intubation is inevitable, which including PaO_2_/FiO_2_ < 85, respiratory arrest, hemodynamic instability, inability to fit the face mask, pneumothorax, vomiting, development of airway bleeding, inability to protect the airway, or copious respiratory secretions.
Morbidities	Mild diseases not stated in the exclusion criteria.	Acute cardiac failure; Acute-on-chronic ARF; Other severe diseases including dilated cardiomyopathy, valvular heart disease, cardiogenic pulmonary edema, implanted cardiac pacemaker, or acute coronary syndrome; systolic arterial pressure < 90 mmHg after optimal fluid therapy; history of chronic obstructive pulmonary disease (COPD) or asthma; impaired consciousness (Glasgow Coma Scale score < 8) [32]; postoperative acute respiratory failure; pregnancy or breastfeeding.
Others	Informed consent to participate in the study signed by the patient or their authorized surrogate decision maker	Lack of consent, do-not-intubate decision, and any other situations where obvious bias are expected.

*ARF* acute respiratory failure, *PaO*
_*2*_
*/FiO*
_*2*_ ratio of the partial pressure of arterial oxygen to the fraction of inspired oxygen, *PaCO*
_*2*_ partial pressure of arterial carbon dioxide, *COPD* chronic obstructive pulmonary disease, *GCS* Glasgow Coma Scale

#### Inclusion criteria

Adult (18 years old ≤ age ≤ 80 years old) immunocompromised patients with severe hypoxemic ARF diagnosed within the last 72 h, who need ventilation support, will be included in the study [26, 27].

Patients will be considered as severe ARF when the ratio of the partial pressure of arterial oxygen to the fraction of inspired oxygen (PaO_2_/FiO_2_) is between 85 and 170 [28, 29] mmHg (adjusted with [PaO_2_/FiO_2_ × (barometric pressure/760)] if altitude is higher than 1000 m [30] similarly hereinafter) or clinically diagnosed with evidence of respiratory distress (intercostal recession or other assisted breathing muscle movements, tachypnea >35/min or dyspnea at rest). PaO_2_ will be measured under oxygen therapy through a Venturi mask, and FiO_2_ will be measured by readings on the mask kit (1,117,005, Intersurgical Ltd., UK).

Patients will considered as immunocompromised when clinically diagnosed as at least one of the following:Hematologic malignancy or solid tumor under chemotherapy or radiotherapy;Solid organ or stem cell transplant;Long-term (>30 days) and high dose steroids (>1 mg/kg/d prednisone equivalent) usage and/or any other immunosuppressive drugs [31];Neutropenia (defined as a neutrocyte count of <1.0 × 10^9^/L) present for at least 48 h.

#### Exclusion criteria

Patients will be excluded from the study when:Age < 18 or >80 years old;Partial pressure of arterial carbon dioxide (PaCO_2_) > 50 mmHg [32] or arterial pH < 7.20;PaO_2_/FiO_2_ > 170 mmHg or PaO_2_/FiO_2_ < 85 mmHg;Patients have been treated with NIV, IMV or high-flow oxygen therapy within 30 days.NIV is contraindicated or IMV is definitely indicated, including PaO_2_/FiO_2_ < 85 mmHg, respiratory arrest, hemodynamic instability, inability to fit the face mask, pneumothorax, vomiting, development of airway bleeding, inability to protect the airway, or copious respiratory secretions;Comorbidity with acute-on-chronic ARF;Comorbidity with acute cardiac failure;HIV positive patients;Comorbidity with other severe diseases, including dilated cardiomyopathy, valvular heart disease, cardiogenic pulmonary edema, implanted cardiac pacemaker, or acute coronary syndrome; systolic arterial pressure < 90 mmHg after optimal fluid therapy; history of chronic obstructive pulmonary disease (COPD) or asthma; impaired consciousness (Glasgow Coma Scale score < 8), [33]; postoperative acute respiratory failure; pregnancy or breastfeeding; Lack of consent, do-not-intubate decision, and any other situations where obvious bias are expected.

### Sample size

The hypothesis of the present trial is that 30-day all-cause mortality in patients treated with NIV will be lower than those treated with IMV. According to previous studies, the mortality rate of ARF immunocompromised patients is from 30% to 90% [1–4]. We used the data from the Fig. 4 of our previous meta-analysis to calculate the sample size, i.e. 30-day mortality in IMV-treated patients of 125/168 (75%) [21], and 85/168 (50%) [21] in NIV-treated patients, 88 patients are needed in each group to establish non-inferiority with 90% power and a 1-sided 5% type I error rate. Assuming that 25% of patients would be lost after the enrollment, thus at least of 236 patients are required.

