#### Interim analysis

Considering a large estimated sample size, two interim analyses are scheduled. Sample sizes of 176 achieve 90% power to detect a difference of 0.25 between the group proportions of 0.50 and 0.75 at a significance level (alpha) of 0.05 using a two-sided z-test with continuity correction. Assuming a dropout rate of 25%, the subjects were required to be 236. The O’Brien-Fleming spending function will be used to determine the test boundaries for 3 sequential tests (Nominal Alpha = 0.000207, 0.012025, 0.046259) [36]. One interim analysis is scheduled after enrollment of 39 patients in both group, and the second analysis after another enrollment of 39 patients in both groups. The independent data and safety monitoring committee (DSMC) consists of one biostatistician and two physicians independent of the present trial. For both interim analyses, the DSMC will monitor and assess results on day 30 mortality, failure of NIV, severe complications and seven-day organ failure as indicated by the SOFA scores. The results of the interim analyses will be kept closed unless DSMC requests premature trial termination based on these results. If the difference of the main outcome, mortality was found statistical difference between groups, then discontinuation ahead will be applied.

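### The sample-size section labels the trial as one-sided 5% non-inferiority without a margin, contradicting the two-sided superiority design that actually yields 88 per group; the sample size itself stands

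*Protocol article*

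**What the plan says.** The Sample size section opens with a directional superiority hypothesis: "30-day all-cause mortality in patients treated with NIV will be lower than those treated with IMV". It takes mortality of 75% with IMV (125/168) and 50% with NIV (85/168) from the earlier meta-analysis, and concludes that "88 patients are needed in each group to establish non-inferiority with 90% power and a 1-sided 5% type I error rate". No non-inferiority margin appears in the article. After allowing for 25% loss, the target is 236.

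The Interim analysis section gives a different basis for the same number. There, 176 patients provide 90% power for a 25-point difference in mortality (50% v 75%), and the test is specified as "at a significance level (alpha) of 0.05 using a two-sided z-test with continuity correction". It adds an O'Brien-Fleming spending function with three tests at nominal levels 0.000207, 0.012025 and 0.046259, and stopping if mortality differs significantly between the groups.

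The Statistical analysis section sets 0.05 for all tests. Its Primary endpoint subsection compares 30-day mortality by χ², with 95% confidence intervals. It describes no non-inferiority test.

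**The concern.** One primary endpoint carries two kinds of claim (non-inferiority and a difference) and two error rates (one-sided 5% and two-sided 5%). These cannot both govern the trial. Two-sided 5% allows 2.5% error in the direction of benefit; one-sided 5% allows twice that.

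The endpoint is mortality and the trial is open-label. If the χ² test is not significant, the Sample size sentence could be cited as apparent pre-specification of non-inferiority, with a margin chosen after the data are known. A reader of the article also cannot tell which hypothesis the 88 per group was meant to serve.

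**Working it through.** **Inputs.** IMV 0.75, NIV 0.50, so d = 0.25 and the mean proportion is 0.625 (Sample size; Interim analysis). Power 90%, z = 1.2816. Allocation 1:1 (Randomization and blinding). One-sided 5%, z = 1.6449 (Sample size). Two-sided 5%, z = 1.9600 (Interim analysis). Loss 25%.

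**Formulas, per group.**
- A (pooled variance under the null, unpooled under the alternative): n = [zα√(2 × 0.625 × 0.375) + zβ√(0.75 × 0.25 + 0.50 × 0.50)]² / d² = [0.6847 zα + 0.6614 zβ]² / 0.0625
- B (pooled variance in both terms): n = 0.46875 (zα + zβ)² / 0.0625
- Continuity correction: n_c = (n/4)[1 + √(1 + 4/(n d))]²

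**1. Reproducing 88 from the Interim analysis inputs (two-sided 5%).**
- A: 2.1896² / 0.0625 = 76.7; corrected 84.5, so 85.
- B: 0.46875 × 3.2415² / 0.0625 = 78.8; corrected 86.6, so 87.
- Three looks: multiplying by 1.016 gives 85.9 (A) and 88.0 (B). The factor is the usual O'Brien-Fleming inflation for three looks. It is my assumption and is not in the article.
- Check without that factor: a simulation using the three stated nominal levels, variance B and the continuity correction gives power 0.898 at 87 and 0.902 at 88. It assumes equally spaced looks; 39/118 and 78/118 per group are close to 1/3 and 2/3.
- Loss: 88/0.75 = 117.3, so 118 per group and 236 in total, as stated.

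An unpooled variance throughout gives 81.4, so 82, for the fixed corrected design. The exact match to 88 therefore depends on the variance formula.

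**2. The Sample size inputs read as superiority (one-sided 5%).**
- A: 1.9738² / 0.0625 = 62.3, so 63; corrected 70.1, so 71.
- With the unrounded rates 125/168 and 85/168: 69, or 78 corrected.
- At 88 per group this test would have power of about 0.97, or 0.95 corrected, not 0.90.

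**3. The Sample size inputs read as non-inferiority (one-sided 5%, margin m assumed because none is stated).** n = 0.4375 × 2.9264² / (0.25 + m)² = 3.747 / (0.25 + m)², uncorrected.

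| Assumed margin | n per group |
|---|---|
| 0 | 59.9, so 60 (68 corrected) |
| 5 points | 41.6, so 42 |
| 10 points | 30.6, so 31 |

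n falls as m rises, so 60 is the uncorrected maximum.

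**4. Non-inferiority under equal mortality, which the article does not assume.** At 88 per group, m = 2.9264 × √(2p(1 − p)/88). This gives 0.19 if both groups have 75% mortality and 0.22 if both have 50%.

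**5. Error rate of the stated boundaries.** Simulated under no difference with the three nominal levels, the overall error is 0.0497 two-sided and 0.0250 in the direction of NIV benefit. The boundaries therefore control two-sided 5%, not one-sided 5%.

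**The case against.** The strongest reply is that the operative plan is a coherent superiority design. Boundaries, stopping rule, significance level and χ² test all point the same way, and 88 fits them. On this view one sentence is wrong, and nothing in the analysis applies a one-sided 5% level or a non-inferiority test. That stands, and it limits the finding to a mislabelled design statement.

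Three further points also stand:
- The hypothesis sentence is directional but does not state sidedness. Two-sided is explicit only in Interim analysis and is implied by the χ² test at 0.05.
- The article is condensed, so a margin might exist in a fuller document. Its absence here is not a separate fault. What remains is the contradiction within the article.
- Non-inferiority is excluded as the source of 88 only under the stated 75% and 50%. Equal mortality with a margin of 19 to 22 points would also give 88, but the article states neither.

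The reply does not remove the contradiction. The Sample size section is where a reader looks for the primary claim and its error rate, and on both it conflicts with the rest of the document.

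**Conclusion.** The Sample size section mislabels the design. Its own rates, power and one-sided 5% level give 63 per group (71 corrected) for superiority and no more than 60 (uncorrected) for non-inferiority at any margin of zero or more. The two-sided continuity-corrected test gives 85 to 87 fixed and about 86 to 88 with three O'Brien-Fleming looks, using a pooled null variance and equally spaced looks. The figures 88, 176 and 236 therefore belong to the Interim analysis design.

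Two stronger readings are tempting and are not supported. A reader might infer that the trial is mis-sized; it is not, because 88 per group fits the two-sided design. A reader might also infer that the sponsor plans to test at a doubled error rate, or to claim non-inferiority after a null result. No analysis section plans either. They are risks that the wording leaves open.

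**What to change.** In the Sample size section, replace "to establish non-inferiority with 90% power" and the one-sided 5% error rate that follows it with wording such as: to show superiority of NIV over IMV (30-day mortality 50% v 75%) with 90% power at an overall two-sided alpha of 0.05, allowing for the three O'Brien-Fleming looks described under Interim analysis. Make no non-inferiority claim from this trial, since no margin is stated.

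The cost is a wording change. The sample size, boundaries and planned test are unchanged. If non-inferiority was in fact intended, rewording is not enough: a margin would have to be justified, and the sample size, boundaries and primary analysis rebuilt around it.

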### Study interventions

Patients included in the study will be randomly allocated into two groups: NIV or IMV group. The participant timeline is listed in Table 2. The study protocol and randomization arms are detailed below and in Fig. 1.

**Table 2 Tab2:** Participant timeline

	Inclusion	Discharge from ICU	Day 30
Informed consent	√		
Eligibility: check inclusion and exclusion criteria	√		
Randomization	√		
Filling of case report forms		√	√
Vital status	√	√	√

